# Outline

## Schema

randomized

REDCap

Female rheumatoid arthritis (RA) patients with moderate disease activity (DAS 28 - ESR is greater than 3.2, less than or equal to 5.1) n=80

Propolis group

n=40

Placebo group

n=40

36 weeks follow-up including post observation

- change in disease activity
- change in clinical test values
- change in sonographic examination of joints
- change in cytokines

primary endpoint

difference in DAS28-ESR change at 24 weeks

## Objective

　To investigate whether RA disease activity can be suppressed by feeding rheumatoid arthritis (RA) patients with propolis, a resinous mixture collected by honey bees from plant sources such as tree buds and sap.

## Subjects

　Eighty female RA patients who met the 2010 ACR/EULAR classification criteria, had moderate disease activity on DAS28-ESR assessment, and had no change in treatment for 3 months.

## Study method

　Eighty female RA patients with moderate disease activity according to the DAS28-ESR will be randomly divided into 40 patients in the propolis group (P group) and 40 patients in the placebo group (C group). P group takes 5 test tablets containing Brazilian propolis (508.5 mg as propolis) per day, and C group takes 5 placebo tablets without Brazilian propolis per day. The DAS28-ESR will be compared in both groups at the time of intervention and after 24 weeks. This will be followed up with a 12-week post-intervention observation period.

## Objective number of enrolled cases and study duration

Planned number of registered patients: 80

Registration period：After approval by the Ethics Review Committee 〜 31 March, 2019

Study period：After approval by the Ethics Review Committee 〜 31 December, 2019

Total study period：After approval by the Ethics Review Committee 〜 30 June, 2020

List of definitions for terms and abbreviations

Terms used in this study protocol

| Terms | Definitions |
| --- | --- |
| TOMORROW study | Total Management of Risk Factors in Rheumatoid Arthritis Patients to Lower Morbidity and Mortality study |

Abbreviations defined in this study protocol

| Abbreviations | Definitions |
| --- | --- |
| P group | Brazilian propolis containing test tablets administration group |
| C group | Brazilian propolis non-containing test placebo tablets administration group |

List of abbreviations for general items

| Abbreviations | Unabbreviated expressions |
| --- | --- |
| RA | rheumatoid arthritis |
| DAS | disease activity score |
| ESR | erythrocyte sedimentation rate |
| ACR | American College of Rheumatology |
| EULAR | European League against Rheumatism |
| IL | interleukin |
| QOL | quality of life |
| MTX | methotrexate |
| DMARDs | disease modifying anti-rheumatic drugs |
| bDMARDs | biological DMARDs |
| csDMARDs | conventional synthetic DMARDs |
| TNF-α | tumor necrosis factor-alpha |
| ADL | activities of daily living |
| CRP | c- reactive protein |
| SDAI | simplified disease activity index |
| CDAI | clinical disease activity index |
| mHAQ | modified health assessment questionnaire |
| WBC | white blood cells |
| RBC | red blood cells |
| Hb | hemoglobin |
| Plt | platelet |
| AST | aspartate transaminase |
| ALT | alanine aminotransferase |
| γ-GTP | γ-glutamyl transpeptidase |
| T-Bil | total bilirubin |
| Cre | creatinine |
| BUN | blood urea nitrogen |
| RF | rheumatoid factor |
| Alb | albumin |
| T-chol | total cholesterol |
| HDL-chol | high density lipoprotein cholesterol |
| TG | triglyceride |
| Na | sodium |
| Cl | chlorine |
| K | potassium |
| Mg | magnesium |
| P | phosphorus |
| Ca | calcium |
| FBS | Fasting blood sugar |
| CCP | cyclic citrullinated peptide |
| MMP | matrix metalloproteinase |
| SF-36 | 36-Item Short-Form Health Survey |
| SJC | swollen joints count |
| TJC | tender joints count |
| GH | global health assessment |
| VAS | visual analog scale |
| NSAID | non-Steroidal Anti- Inflammatory Drug |
| BMI | body mass index |
| REDCap | research electronic data capture |
| CRC | clinical research coordinator |

# Study background

　Rheumatoid Arthritis (RA) is an autoimmune disease whose true cause is unknown. It is thought

that an autoimmune response is initiated by exposure to environmental factors such as smoking and periodontal disease in addition to some genetic background. When an autoimmune response is

initiated, inflammation in the joints or systemically causes swelling and pain in the joints,

which progresses to destruction and deformity of the joints. In RA, osteoclasts are activated by

inflammatory cytokines, resulting in bone destruction. The prevalence of RA in adults is about 0.5-1% worldwide, and it occurs mostly in women in their 30s to 50s, with more than 700,000 patients in Japan. Despite this large number of RA patients, the detailed pathogenesis of RA remains

unknown, and there is currently no fundamental treatment strategy. Currently, the main treatments for RA symptoms such as joint pain, swelling, inflammation, and other disease activity include

pharmacotherapy and surgical treatments, with pharmacotherapy being the cornerstone of RA

treatment. Medications include disease-modifying anti-rheumatic drugs (DMARDs) such as

methotrexate (MTX), biologics that molecularly target inflammatory cytokines such as infliximab, a monoclonal antibody against TNF-α (tumor necrosis factor-alpha), and tocilizumab, an IL-6

(interleukin-6) receptor antibody. In addition, there are corticosteroids and other medicines that aim to reduce inflammation. The problems with medications are, of course, that they have various side effects, that biologics and other medicines are expensive and not available for all patients, and that they may not be equally effective for all patients. Therefore, many patients continue to receive treatment without reaching the current treatment goal of remission.

　The health food used in this study is a test meal containing Brazilian propolis from Yamada Bee Company, Inc. Propolis is a sticky resinous substance made by honeybees by collecting plant buds, sap, and pollen and mixing them with saliva and beeswax that they secrete. The main plant sources

of the propolis bulk of the extraction source of the Yamada Bee Company, Inc. Brazilian propolis-

containing test food is Baccharis dracunculifolia collected in the state of Minas Gerais, Brazil. For arthritis, Brazilian propolis has been reported to contribute to the suppression of disease

activity in a mouse rheumatoid arthritis model. As a mechanism, it has been reported that Brazilian propolis suppresses the phosphorylation of STAT3 (signal transducer and activator of

transcription 3), which is necessary for the differentiation process of naive helper T cells into IL-17 producing helper T cells (Th17 cells), and suppresses IL-17 production. Based on the above, propolis may contribute to the suppression of disease activity in RA, which may lead to the

development of new RA therapeutics. However, currently, there are only research results from

animal experiments in a mouse rheumatoid arthritis model, and the suppressive effect of propolis

on disease activity in humans is unknown. Therefore, in this study, we would like to clinically

examine how propolis administration changes the disease activity of RA patients. Since the disease activity index includes the patient's own evaluation of pain and disease activity, blinding is

essential, and we would like to prepare propolis-free test tablets and conduct them as a double-

blind randomized trial.

# Study aims

Object disease patients: 80 female RA patients who met the 2010 ACR/EULAR classification criteria. Test food: Test tablets containing Brazilian propolis

Evaluation items：

・Anthropometry: height, weight, waist circumference

・Disease activity：DAS28-ESR・DAS28-CRP・SDAI・CDAI

・ADL：mHAQ

・Laboratory data: General items（WBC, RBC, Hb, Ht, Plt, AST, ALT, γ-GTP, T-Bil, Cre, BUN, CRP, ESR, RF, TP, Alb, T-chol, HDL-chol, TG, Na, Cl, K, Mg, P, Ca, FBS, special items（anti CCP antibody, MMP-3, IL-6, IL-17, IL-10）

・Blood pressure

・Lifestyle survey: smoking status, alcohol consumption, exercise habits, sleep time, supplement use and type

・QOL:SF－36

・Objective arthritis assessment: sonographic examination of joints

　Eighty female RA patients with moderate disease activity by DAS28-ESR will be divided into two groups: 40 patients treated with Brazilian propolis (P group) and 40 patients treated with placebo balls (C group). In doing so, allocation will be by double-blind randomization using a stratified replacement block method, with facilities in strata. The test food is manufactured at Yamada Bee Company, Inc., Ltd. for 40 people in each group, plus 5 people in the reserve group, for a 3-month supply of 5 tablets per day x (84 days + 7 days in reserve) x 45 people = 2,0475 tablets. This is one set and we plan to make two sets for 6 months. The P group will take 5 tablets of the test diet containing Brazilian propolis (508.5 mg as P) per day, and the C group will take 5 tablets of the placebo diet without Brazilian propolis per day. In both groups, DAS28-ESR will be compared at 0, 12, 24, and 36 weeks, and the above evaluation items will also be compared.

The purpose of this study is to clarify whether Brazilian propolis has an suppressive effect on disease activity not only in mouse RA models but also in RA patients.

# Overview of the test foods

## Test foods

See the test food summary for details.

## Anticipated adverse reactions and, in the case of medical devices, anticipated defects

See the test food summary for details.

# Diagnostic criteria and stage/type classification of target diseases

The diagnosis of RA is based on the 2010 ACR/EULAR classification criteria.

The DAS28-ESR classification of disease activity for RA is as followsDAS28-ESR

Less than 2.6: Remission

2.6 or higher, 3.2 or lower: low disease activity

Greater than 3.2, less than 5.1: moderate disease activity

Greater than 5.1: High disease activity

DAS28-ESR = 0.56 × √28TJC + 0.28 × √28SJC + 0.76In(ESR) + 0.014 × GH-VAS

SJC and TJC are assessments of 28 joints in the body.

# Subject patients

　Female RA patients with moderately active disease (greater than or equal to 3.2 and less than or equal to 5.1) on the DAS28-ESR at the time of intervention. The inclusion criteria were patients with moderate disease activity, because the therapeutic goal for RA is at least low disease activity or less (DAS-ESR 3.2 or less), and higher disease activity (greater than 5.1) should be selected for more aggressive pharmacological treatment.

## Inclusion criteria

　Patients who meet all the following criteria should be selected for inclusion.

1. RA patients meeting the 2010 ACR / EULAR classification criteria (irrespective of disease duration)
2. Age: Patients who are between 30 and 70 years old at the time of obtaining consent
3. Gender：Female
4. Moderate disease activity (DAS28-ESR is greater than 3.2, less than or equal to 5.1)
5. After receiving sufficient explanation for the participation of this study, patients who obtained document consent by the patient's free will with sufficient understanding.
6. Administration of bDMARDs and csDMARDs is constant over 12 weeks before intervention
7. The dose of NSAID and steroid (predonisolone equivalent 10 mg / day or less) dose is also constant for 12 weeks or more before consent acquisition
8. Outpatient

［Evidence of setting］

1) Because this is a study of RA patients and the duration of illness is not expected to

affect the results of the study.

2) This is due to the epidemiological background of RA. Because most outpatients are between

30 and 70 years of age.

3) We restricted the study to females, much of the population, so as not to be influenced by

gender.

4) Because we believe that if the disease activity is below low disease activity, therapeutic target is reached, and high disease activity is not the target of the health food.

5）From an ethical perspective.

6)-7) To exclude the effect of medication on disease activity, as it has a strong impact on

patients treated with medications for RA.

8) To perform disease assessment every three months.

## Exclusion Criteria

Patients who meet any of the following criteria will be excluded.

1. Patients who cannot come to the examination on a regular basis
2. Patients with undifferentiated arthritis
3. Patients taking propolis as a supplement within 4 weeks before consent acquisition
4. Patients with significant obesity (BMI 30 or more)
5. Patients with abnormalities in liver function (AST or ALT more than 3 times higher than normal upper limit)
6. Patients with abnormal renal function (BUN 25 mg / dL or more or serum creatinine 2.0 mg / dL or more)
7. Patients who are pregnant or lactating
8. Patients with food allergy history
9. Others, patients judged by doctors as inappropriate as subjects

［Evidence of setting］

1) For impact on efficacy assessment and safety considerations

2) To evaluate the efficacy in RA patients

3)-4) Because of its impact on efficacy assessment

5)-9) For safety considerations

# Case registration and assignment

Assignment and coding of study foods: double-blind

After the test and placebo foods are manufactured at Yamada Bee Company, Inc., they are packaged at the Institute for Bee Products & Health Science in sachets containing five tablets for one day and 91 sachets for 84 plus seven days as a three-month supply for one person. The Institute for Bee Products & Health Science will then randomly assign study food allocation codes to the entire set (40 participants per group + 5 spares x 2 groups = 90 participants) and send the allocation list only to the REDCap randomization staff. In the Institute for Bee Products & Health Science, 1) All test tablets are coated with white color to ensure the indistinguishability of the test food. (2) The test food assignment code list will be kept by the Institute for Bee Products & Health Science, and REDCap test food assignment and coding staff, until the key is opened, and will not be disclosed to any other person. Keys will not be opened until the study is completed and the data for each case is fixed, except in the case of emergency evacuation. In addition, one unit (one set) of test food shall be used for one case.

Method of enrollment of subjects: Randomization

Prior to subject enrollment, the principal investigator or subcontracting physician will provide the person who is to be the subject of the study with an explanatory document that has been approved by each medical institution (the explanatory document in the Appendix or an explanatory document modified by each medical institution). Then, in principle, the contents of the "Ethical Guidelines for Medical Research Involving Human Subjects" will be explained in detail orally, and free and voluntary consent for participation in the study will be obtained in writing. When obtaining consent, the prospective subject should be given sufficient time and opportunity to ask questions to determine whether to participate in the study, and questions should be fully answered. After obtaining consent, the required fields are entered into the subject registration screen in the REDCap system to confirm eligibility. Once eligibility has been confirmed, random allocation of test subjects will be conducted by inputting information from the test food allocation screen in the REDCap system. The distribution of the test foods will be conducted on the same day.

Registration system: REDCap system

URL：ocu.jp/redcap

# Study plan

## Study type and design

The study design was a multicenter, double-blind, randomized, parallel-group, placebo-controlled trial. It is known as the method with the highest level of evidence in verifying the effects of foods.

## Study outline

[figure not shown]

## Duration of subject's participation in the study

All patients up to 40 weeks follow-up.

## Dosage and administration of the test food, and duration of administration

　P Group will receive 5 test tablets containing Brazilian propolis daily, and C Group will receive 5 placebo tablets daily. No time of administration is specified. The test food will be provided in sachet packages of five tablets each, with the intention of ingesting five tablets at a time, but it will be acceptable for study participants to ingest them in divided portions. If patients do not take 5 tablets in a day, do not take them the next day and return the whole sachet at next visit. No more than five tablets per day were to be taken. The entire sachet will be collected at each visit, so any leftovers should be checked and recorded at this time. The administration period should be 24 weeks.

［Evidence for setting the dose and duration of administration］

　The dose of the test food containing Brazilian propolis used in this study was 5 tablets (508.5 mg of Brazilian propolis extract powder), which is the midpoint of the 4-6 tablets per day set as the standard dose by Yamada Bee Company, Inc.

## Provisions on concomitant medications (therapies)

１）Concomitant medications (therapy): No change in concomitant medications will be made if possible during the 24 weeks of the study. However, this does not apply if the disease

activity cannot be adequately controlled. Biologics can also be used in combination as

long as they are given at a constant dose starting 12 weeks before the intervention.

２）Prohibited medication (therapy): Propolis intake (purchased at own cost)

３）Restricted concomitant medications (therapy): None listed

４）Concomitant medications that should be used with caution (therapy): Warfarin potassium

５）Allowed concomitant medications (therapy): None listed

## Methods of dose reduction and withdrawal (study medicine adjustment methods)

　　　Since this study deals with food, there is no method for dose reduction or drug withdrawal.

## Control and delivery procedures for test foods

Each facility will receive a set of test foods and placebo in a ratio of 1:1, including spares, from the Institute for Bee Products & Health Science (26 for Osaka City University, 32 each for Shirahama Hamayu Hospital and Kitade Hospital, with the Kitade Hospital portion sent to Shirahama Hamayu Hospital). All of them are higher than the objective number of cases, so we believe there will be no shortage. Brazilian propolis tablets and placebo tablets will be managed by CRC. After randomization and allocation, a 12-week supply will be handed to each patient at the start of administration and at 12 weeks, respectively.

Storage location: Investigational product control room (for Osaka City University) and Search Institute for Bone and Arthritis Disease, Shirahama Foundation for Health and Welfare (for Shirahama Hamayu Hospital and Kitade Hospital)

Person responsible for storage: [name], Principal Investigator

## Intake guidance information

- Time of intake: Not specified
- Intake method: Take 1-5 spheres with water without chewing.
- If forget to take a dose: skip that day's dose and the next day and thereafter, take as usual.
- Storage method: Store at room temperature
- How to return the remaining samples and containers: Bring them to the outpatient clinic at 12 weeks and 24 weeks.

## Actions after the study (or "post-treatment")

Strive to ensure that subjects receive the best possible prevention, diagnosis, and treatment based on the results of the study even after the study is completed.

## Preservation of samples, etc. and use of samples, etc. by other institutions, etc.

- Storage: Serum for cytokine assay will be stored at -80°C until assay at Osaka City University and Search Institute for Bone and Arthritis Disease.
- Method of use: All measurements are performed at LSI Medience, Inc. after collection ofall samples.
- Storage period: until measurement data is finalized
- Administrator: [name], study supervisor
- Disposal method: Anonymized and disposed of after data is finalized
- Instruct and manage researchers, etc., to ensure that information, etc., is accurate,

and manage samples and information, etc., obtained from human subjects as necessary to prevent leakage, mixing, theft, loss.

- Report to the hospital director on the status of management in accordance with the procedure manual for the storage of samples and information obtained from human bodies.

# Observation and examination items and schedule

The following surveys will be conducted according to the timetable

1. Patient's background

　Medical record number, patient name, gender, date of birth, comorbidities, medical history, current medical history, previous treatment, concomitant medications (concomitant therapy and current treatment details), lifestyle (smoking status, alcohol consumption, exercise habits, sleep time, supplement use and type). However, medical record numbers and patient names are not entered into the REDCap (case report form).

1. Confirmation of intake of test foods

　The intake status during the study period will be assessed in percentage and recorded in REDCap. Participants will return all samples, including unused packaging materials, to the implementing medical institution at each visit. The CRC calculates the intake rate based on the number of tablets distributed and returned. For each case, the intake of the test food from the day after the previous visit to the day of the visit will be investigated and compliance with the intake will be requested.

1. Confirmation of subjective symptoms and other findings, evaluation of disease activity

Based on the questionnaire, palpation, and laboratory data, disease activity is quantified according to the following formula.

DAS28-ESR = 0.56 × √28TJC + 0.28 × √28SJC + 0.76In(ESR) + 0.014 × GH-VAS

DAS28-CRP = 0.56 × √28TJC + 0.28 × √28SJC + 0.36In(CRP × 10 + 1 ) + 0.014 × GH-VAS + 0.96

SDAI = 28TJC + 28SJC + PtGH-VAS(patient) + DrGH-VAS(physician) + CRP (mg/dl)

CDAI = 28TJC + 28SJC + PtGH-VAS(patient) + DrGH-VAS(physician)

1. Confirmation of adverse events and side effects: Describe in the medical record and case report the details, including abnormalities in various laboratory data, time of occurrence and disappearance, severity, treatment, outcome, assessment of severity, and relationship to the study food, and follow up as necessary. The severity is defined as 1) mild: administration can be continued without treatment, 2) moderate: administration can be continued with some treatment, and 3) severe: administration should be stopped or discontinued.
2. Height, weight, and waist circumference
3. Blood pressure and pulse rate
4. Hematological tests

WBC, RBC, Hb, Ht, Plt

1. Blood biochemistry test

AST, ALT, γ-GTP, T-Bil, Cre, BUN, CRP, ESR, RF, TP, Alb, T-chol, HDL-chol,TG, Na, Cl, K, Mg, P, Ca, FBS

1. Other specific tests

・anti-CCP antibody、MMP-3、IL-6、IL-17、IL-10

　Subcontractor name: LSI Medience Co.Ltd.

・QOL：SF－36

　　・ADL：mHAQ

・Disease activity：DAS28-ESR・DAS28-CRP・SDAI・CDAI

・Sonographic examination of joints：sonographic examination of synovitis in 7 joints on the side with stronger symptom at baseline (unchanged during the observation period) (2nd and 3rd metacarpophalangeal (MP) joints, 2nd and 3rd proximal interphalangeal (PIP) joints, wrist, and 2nd and 5th metatarsophalangeal (MTP) joints) using both grayscale (GS) (grade 0–3) and power-Doppler (PD) scale (grade 0–3)

Timetable

| Item | pre-  observation | Start administering the test foods | Administration period | End of test food administration | post-  observation |
| --- | --- | --- | --- | --- | --- |
| Period | Before  1-4 weeks | 0 week | After 12 weeks  (±7day) | After 24 weeks  (±7day) | After 12 weeks |
| Medical Examination | 1 | 2 | 3 | 4 | 5 |
| Consent obtain | ○ |  |  |  |  |
| Check patient background | ○ |  |  |  |  |
| Test food administration |  |  |  |  |  |
| Subjective symptoms and other findings | ○ | ○ | ● | ● | ● |
| Observation of adverse events^a^ |  |  | ● | ● | ● |
| Anthropometry^b^ |  | ○ |  | ● |  |
| Blood pressure and pulse measurement |  | ○ | ● | ● | ● |
| Hematological examination |  | ○ | ● | ● | ● |
| Blood Biochemistry Test |  | ○ | ● | ● | ● |
| Sonographic examination of joints |  | ○ | ● | ● | ● |
| QOL assessment |  | ○ |  | ● |  |
| Disease activity assessment^c^ | ○ | ○ | ● | ● | ● |

　Items marked with an asterisk ○ are items to be performed before administration of the test food, and items marked with an ● are items to be performed after administration of the test food.

a: Adverse events are all events that are undesirable, such as side effects, regardless of whether they are causally related to the test food.

b: Measure height, weight, and abdominal circumference as anthropometry.

c: Evaluate DAS28-ESR, DAS28-CRP, SDAI, and CDAI for disease activity.

Blood tests should be performed under fasting conditions to rule out the effects of diet.

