# Handling of adverse events

## Response to subjects in an adverse event

　An "adverse event" is any unfavorable or unintended sign, symptom, or illness that occurs when a test food is administered, regardless of whether it is causally related to the test food.

When an adverse event is recognized, the principal investigator or sub-investigator should immediately take appropriate treatment and record it in the medical record and case report without any discrepancy.　In addition, subjects will be informed if the administration of the test food is discontinued or if treatment for adverse events becomes necessary. If it is necessary to identify the test food as an emergency evacuation, request the person in charge of test food allocation and coding through the principal investigator, etc., to disclose the results of opening the package for the case. When the occurrence of a serious adverse event is recognized, all serious adverse events will be promptly reported to the hospital director, regardless of whether there is a causal relationship with the research

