## Secondary endpoints

1. DAS28-CRP, SDAI and CDAI at week 12, 24 and 36.
2. QOL evaluated by the change of the score by SF-36 at week 24.
3. The change of ADL evaluated by mHAQ at week 12, 24 and 36.
4. The change of sonographic total scale of hand and foot joint at week 12, 34 and 36.
5. Adverse events requiring discontinuation of the test food up to 24 weeks after starting ingestion.
6. Severe adverse events up to 36 weeks after starting ingestion.
7. All adverse events up to 36 weeks after starting ingestion.

【Evidence of setting】

1） Other methods of assessing disease activity other than the DAS28-ESR, each of which has its own advantages and disadvantages, should also be used.

2) As a general QOL assessment tool for subjects, the SF-36 has been reported in numerous articles due to its simplicity and reliability. We will evaluate the effect of QOL improvement associated with suppression of disease activity.

3) It is the gold standard for the assessment of ADL in RA patients not only in ACR/EULAR but also worldwide. We will evaluate the improvement of ADL with the suppression of disease activity.

4) Obtain a more objective assessment because disease activity assessment includes many subjective items.

5-7) To evaluate the safety of test foods.

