## Considerations for safety and disadvantage

In the case of an adverse event, appropriate medical examination and treatment should be performed promptly. If there is no improvement and moderate to severe adverse events persist, discontinue the study for the subject.

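### Adverse event severity is graded by whether the test food can go on, so the severe grade has no criterion in the 12 weeks after the food ends and nearly repeats another endpoint before that

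*Protocol*

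**What the plan says.** Section 8, under confirmation of adverse events, requires a severity for each event and gives the protocol's only severity scale. The lowest grade reads "The severity is defined as 1) mild: administration can be continued without treatment". The other two read "2) moderate: administration can be continued with some treatment, and 3) severe: administration should be stopped or discontinued".

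On timing, section 7.4 states "The administration period should be 24 weeks", and the study method in the outline adds 12 weeks of observation after the intervention. The timetable in section 8 marks adverse event observation at the week 12, week 24 and post-observation visits.

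Two safety endpoints in 12.2 matter here. Endpoint 5 is "Adverse events requiring discontinuation of the test food up to 24 weeks after starting ingestion". Endpoint 6 is "Severe adverse events up to 36 weeks after starting ingestion".

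Section 17.5 brings the grades into a rule for the subject: "If there is no improvement and moderate to severe adverse events persist, discontinue the study for the subject". Section 9 separately lists difficulty in continuing because of adverse events, and the physician's judgement, as grounds for discontinuation. It does not refer to the grades.

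**The concern.** A severity grade should describe how bad the event was. What was done with the study product is a separate fact. Here the grade is defined through the second, with three consequences.

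- The top grade depends on there being intake to stop. Once the food has ended, a site grading an event at the post-observation visit has no written criterion for *severe*.
- While the food is being taken, *severe* and *requiring discontinuation of the food* come from almost the same judgement, so two endpoints carry little more information than one.
- Section 17.5 uses the grades as a trigger for discontinuation, although the grades already contain a statement about continuing or stopping.

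At stake is whether the severity data mean the same thing at the three institutions and throughout the 36 weeks.

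**Working it through.** **Inputs**

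- End of the endpoint 6 window: week 36 (12.2).
- Length of intake: 24 weeks (7.4).
- Post-intervention observation: 12 weeks (study method in the outline; last column of the timetable).

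**Off-food share of the window**

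- Off-food weeks = endpoint window − intake period = 36 − 24 = 12. This reproduces the protocol's own 12-week post-observation period.
- Share = 12 / 36 = 0.333, or 33%.

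This is for a patient who takes the food for the full 24 weeks.

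**Can each grade be assigned?**

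| Grade (section 8) | What decides it | Weeks 0–24 | Weeks 24–36 |
| --- | --- | --- | --- |
| Mild | intake can go on; no treatment needed | yes | partly: need for treatment can still be judged |
| Moderate | intake can go on; some treatment needed | yes | partly: need for treatment can still be judged |
| Severe | intake should stop | yes | no: there is no intake to stop |

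The boundary between mild and moderate survives off food because need for treatment separates the two. The boundary between moderate and severe does not: it rests entirely on the action on the food.

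**Endpoint 5 against endpoint 6 in weeks 0–24**

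- Endpoint 5: events that require the food to be discontinued.
- Endpoint 6 through the section 8 scale: events for which the food should be stopped or discontinued.

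The two sets are nearly the same. The severe grade may be slightly wider if stopping includes a temporary interruption. So endpoint 6 adds little before week 24 and has no usable criterion after it.

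**If endpoint 6 means serious**

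Section 14.3 plans Kaplan-Meier curves and a Cox model for *serious* events, and 10.2 defines those by outcome (death, threat to life, hospitalisation and so on), without reference to intake. On that reading endpoint 6 can be observed to week 36 and is distinct from endpoint 5. The severity grade that section 8 requires for each event is still undefined at its top level off food, and the words in 12.2 and 14.3 need to be made the same.

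**Section 8 against 17.5**

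| Event | Section 8 | Section 17.5 |
| --- | --- | --- |
| Moderate | intake can go on, with treatment | subject discontinued if the event persists without improvement |
| Severe | intake should stop | named under the same condition of persistence without improvement |

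Section 8 speaks of administration and 17.5 of the study for that subject. The protocol does not say how the two relate, nor whether a persisting moderate event is to be regraded.

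**The case against.** The strongest reply is that this is a wording matter in exploratory safety outcomes. Section 14.3 plans a frequency table of adverse event occurrence by group and names no table by severity. Section 9 already records the date and reason of discontinuation in the case report form, so endpoint 5 can largely be derived without the grade. The primary analysis is untouched. All of this stands and limits the weight of the point. It does not supply the missing criterion for an endpoint that, as written, counts severe events to week 36.

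A reader might also infer several stronger things that the protocol does not support:

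- *That 17.5 flatly contradicts section 8.* Saying that intake can continue is permissive, so a later stop for lack of improvement is compatible with it. Nor does 17.5 say that a severe event leads to discontinuation only if it persists. Section 9 leaves room for adverse events and for the physician's judgement. What remains is an unexplained tension.
- *That 7.6 forbids withdrawal.* Its statement that "there is no method for dose reduction or drug withdrawal" stands under a heading on adjustment methods and is naturally read as concerning dose adjustment. Sections 9, 10.1 and 17.5 all provide for stopping.
- *That events after week 24 are not adverse events at all.* Section 10.1 speaks of "any unfavorable or unintended sign, symptom, or illness that occurs when a test food is administered", but the timetable schedules observation off food and its footnote on adverse events sets no such limit. Aligning the two wordings is a minor clarification.
- *That endpoints 5 and 6 coincide completely, or that a trivial event becomes severe because the food happened to be stopped.* The scale asks whether intake should be stopped, not whether it was, and may cover interruption.
- *That nothing can be graded after week 24.* Need for treatment can still be judged.

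**Conclusion.** The point holds in a limited form. The only severity scale in the protocol defines its top grade by action on the food, so that grade has no applicable criterion in weeks 24 to 36, which is 12 of the 36 weeks (33%) of endpoint 6. Before week 24 it largely duplicates endpoint 5.

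The consequence for endpoint 6 assumes that *severe* there refers to the section 8 scale. If *serious* was meant, endpoint 6 is observable, and the defect falls on the grade recorded for each off-food event. The tension between sections 8 and 17.5 exists on either reading and calls for reconciliation. The effect is confined to secondary safety outcomes. It is worth correcting because sites apply the grade at the visit, and a later analysis cannot recover an intensity that was never recorded.

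**What to change.** 1. In section 8, define mild, moderate and severe by the intensity of the event, independently of what is done with the food.
2. Add a separate eCRF field for action taken with the test food: continued, stopped, or not applicable after week 24.
3. Derive endpoint 5 from that field. State in 12.2 and 14.3 whether endpoint 6 is *severe* or *serious*. If *severe* is kept, derive it from the new grade; if *serious*, from the 10.2 definition.
4. Reconcile sections 8, 9 and 17.5 on discontinuation for adverse events so that one rule stands. Which rule is for the sponsor to decide.
5. As a minor clarification, align the adverse event definition in 10.1 with the timetable footnote, so that the off-food weeks are plainly covered.

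The cost is a wording amendment, one eCRF field and a notice to sites about the new grading. Sample size and the primary analysis do not change.
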